# Utility of Abdominal Drain in Gastrectomy (ADiGe) Trial: study protocol for a multicenter non-inferiority randomized trial

**DOI:** 10.1186/s13063-021-05102-1

**Published:** 2021-02-17

**Keywords:** Gastric cancer, Gastrectomy, Abdominal drain, Drainage, Randomized controlled trial

## Abstract

**Background:**

Prophylactic use of abdominal drain in gastrectomy has been questioned in the last 15 years, and a 2015 Cochrane meta-analysis on four RCTs concluded that there was no convincing evidence to the routine drain placement in gastrectomy. Nevertheless, the authors evidenced the moderate/low quality of the included studies and highlighted how 3 out of 4 came from Eastern countries. After 2015, only retrospective studies have been published, all with inconsistent results.

**Methods:**

ADiGe (Abdominal Drain in Gastrectomy) Trial is a multicenter prospective randomized non-inferiority trial with a parallel design. It aimed to verify whether avoiding routine use of abdominal drain is burdened with complications, particularly an increase in postoperative invasive procedures. Patients with gastric cancer, scheduled for subtotal or total gastrectomy with curative intent, are eligible for inclusion, irrespective of previous oncological treatment.

The primary composite endpoint is reoperation or percutaneous drainage procedures within 30 postoperative days. The primary analysis will verify whether the incidence of the primary composite endpoint is higher in the experimental arm, avoiding routine drain placement, than control arm, undergoing prophylactic drain placement, in order to falsify or support the null hypothesis of inferiority. Secondary endpoints assessed for superiority are overall morbidity and mortality, Comprehensive Complications Index, incidence and time for diagnosis of anastomotic and duodenal leaks, length of hospital stay, and readmission rate.

Assuming one-sided alpha of 5%, and cumulative incidence of the primary composite endpoint of 6.4% in the control arm and 4.2% in the experimental one, 364 patients allow to achieve 80% power to detect a non-inferiority margin difference between the arm proportions of 3.6%. Considering a 10% drop-out rate, 404 patients are needed. In order to have a balanced percentage between total and subtotal gastrectomy, recruitment will end at 202 patients for each type of gastrectomy. The surgeon and the patient are blinded until the end of the operation, while postoperative course is not blinded to the patient and caregivers.

**Discussion:**

ADiGe Trial could contribute to critically re-evaluate the role of prophylactic drain in gastrectomy, a still widely used procedure.

**Trial registration:**

Prospectively registered (last updated on 29 October 2020) at ClinicalTrials.gov with the identifier NCT04227951.

**Supplementary Information:**

The online version contains supplementary material available at 10.1186/s13063-021-05102-1.

## Introduction

### Background and rationale

Prophylactic drain placement after gastrectomy has been advocated until the last few years as the main tool for early diagnosis and treatment of surgical intra-abdominal complications, especially with regard to anastomotic or duodenal stump leakages. Evidence against routine drain use after colorectal resection [1, 2] raised the interest on this argument. There was also interest for upper gastrointestinal surgery and, in 2015, a Cochrane meta-analysis [3] on 4 RCTs concluded that there was no convincing evidence to the prophylactic drain placement after gastrectomy. Nevertheless, the authors evidenced the moderate/low methodological quality of the included studies and highlighted how 3 studies out of 4 came from Eastern countries [3]. Moreover, randomization was never mentioned in 1 of the 4 articles, classified as RCTs. After 2015, other retrospective studies have been published, but most of them included a small number of patients and heterogeneous types of surgery, including multi-visceral and R2 resection [4–7]. Our study group recently published an updated meta-analysis including both RCTs and cohort studies, comparing the use of prophylactic drain with drain avoidance [8]. The results suggest that skipping drainage can reduce morbidity and length of stay, without affecting other major surgical outcomes. However, as for the Cochrane meta-analysis, the strength of this evidence is blunted by the limited quantity and quality of data available. Waiting for further evidence, the use of prophylactic abdominal drain after gastrectomy is currently left up to the surgeon’s preference.

### Objectives

The aim of the study is to evaluate whether avoiding prophylactic drain placement in gastrectomy results in an increase of postoperative invasive procedure (reoperation or percutaneous drain placement) compared with routine procedure, i.e., prophylactic drain placement. If this inferiority hypothesis was rejected, avoiding drain placement would be favored as drain placement is a possible harmful procedure. Moreover, the study will be performed on Western patients, who have been less extensively studied so far than Eastern patients.

### Trial design

The design is a multicenter non-inferiority randomized controlled trial with a parallel design, conducted on behalf of the Italian Research Group for Gastric Cancer (GIRCG). The sponsor of the study is Verona University Hospital that appointed a steering committee including members belonging to the sponsor itself and the GIRCG. The study has been approved by the Institutional Review Board (IRB) at the central coordinating center and has to be approved at each of the participating hospitals. The ADiGe trial was registered at ClinicalTrials.gov #NCT0422795. The protocol adheres to the Standard Protocol Items: Recommendations for Interventional Trials (SPIRIT) guidelines.

## Methods: Participants, interventions, and outcomes

### Study settings

All hospitals belonging to the GIRCG are eligible to participate in the ADiGe Trial, irrespective of their hospital volume. A total of 9 centers applied to participate, and, at the time of this publication, the study has already been approved by the local IRB of each center (Verona University Hospital, the leading Center, Orbassano Hospital of Turin, San Raffaele Hospital of Milan, Morgagni Hospital of Forlì, Federico II University Hospital of Naples, Niguarda Hospital of Milan, S. Orsola-Malpighi Hospital of Bologna, Parma University Hospital, Modena University Hospital).

### Eligibility criteria

All consecutive patients that undergo total (TG) or subtotal gastrectomy (STG) with curative intent, for histologically proven gastric cancer or esophago-gastric junction cancer (Siewert type II or III), are eligible in participating centers from the beginning of the study until they reach the accrual number for each arm.

#### Inclusion criteria

Esophageal involvement ≤ 2 cmPatients planned for upfront surgery or treated with a neoadjuvant/perioperative chemotherapy or chemo-radiotherapyOpen, hybrid, laparoscopic, or robotic approachAll types of anastomoses (circular stapled, linear stapled, hand sewn)

#### Exclusion criteria

Refuse to sign informed consentAge < 18Severe heart disease (Heart failure New York Heart Association - NYHA Class IV)Severe liver disease (Child-Pugh ≥ B7) [9]PregnancyMetastatic diseaseGastrectomy performed in an emergency conditionPalliative surgeryOperation different from total or subtotal oncological gastrectomy (e.g., pylorus-preserving, proximal gastrectomy)< D1 lymph nodal dissection according to the Japanese Gastric Cancer Association guidelines 5th edition [10]Reconstruction different from Roux-en-Y or Billroth IIMultiple organ resection (except for cholecystectomy)Gastric cancer with duodenal involvementIntraoperative hyperthermic intraperitoneal chemotherapy

We included in the trial patients with limited esophageal involvement defining a threshold of 2 cm in order to guarantee a proper oncological treatment. According to the available evidences, a tumor that invades the esophagus for more than 2 cm has an increased incidence of mediastinal nodal involvement, thus requiring a thoracic approach [11, 12].

Compared to 3 RCTs already published on this topic [13–15], we also included patients that undergo neoadjuvant/perioperative therapies, as these treatments are currently the standard of care for locally advanced gastric tumors. A 2018 meta-analysis on 9 studies evidenced that neoadjuvant therapy is not associated with increased morbidity and mortality as compared to upfront surgery [16]. These results have been confirmed also in a recent propensity score matching analysis [17].

No restriction on a previous abdominal surgery has been planned since data available in literature suggest no correlation with postoperative morbidity [18, 19]. Moreover, considering that minimally invasive and open surgery outcomes are nowadays comparable, we decided to include both types of approaches.

We included only Roux-en-Y and Billroth II reconstruction because they have similar vulnerabilities: the anastomosis and the duodenal stump. On the other hand, Billroth I reconstruction has different morbidity due to the lack of a duodenal stump and a direct suture between the gastric remnant and the duodenum.

Cholecystectomy was not considered as an exclusion criterion because some evidence suggests its utility in a subset of patients undergoing gastrectomy [20], and it seems not to add morbidity or mortality to the main operation [21].

### Who will take informed consent

Patients eligible for participation are informed about the trial by one of the surgeons during the preoperative visit at the outpatient clinic. Patients can agree to participate until the day before the operation by signing the informed consent.

### Intervention description

#### Operation and intraoperative dropout

Randomized patients included in the control group (group A) receive one abdominal drain (any type of drainage is allowed) placed below the liver, passing by the duodenal stump with the apex posterior to the esophago-jejunal or gastro-jejunal anastomosis. No drainage is placed in patients assigned to the experimental group (group B). Towards the end of the operation the leading surgeon can classify a patient as an intraoperative dropout before knowing the randomization arm, if one or more of the following criteria are met:
Intraoperative finding of non-radically resectable disease (R2 resection—gross residual disease with gross residual tumor that was not resected) [22]Need for unplanned multiple organ resection (except for cholecystectomy)High risk anastomosis defined as intraoperative test (e.g., methylene blue or pneumatic test) positive for leak or intraoperative evidence of a positive resection margin.Other intraoperative complication that has to be specified in the case report form (unintended intraoperative damage to major vessels and/or organs requiring reconstruction or resection, intraoperative bleeding requiring urgent transfusion, unexpected medical conditions interrupting or changing the planned procedure [23]).

#### Postoperative procedure

All patients follow the usual postoperative pathway of each participating center except for abdominal drain management. Prophylactic drain in group A patients is daily evaluated checking for suspicious debt. In patients with a normal debt, a methylene blue test (the patient is asked to drink 200 ml of water/tea with 5 ml of methylene blue) is performed on postoperative day (POD) 4 and the test is considered negative if no blue staining of drain output is apparent within 60 min (the 200-ml colored solution stays in the esophageal/gastric lumen and this is considered as an indirect sign of the absence of an anastomotic leak). After the blue test is confirmed as negative, the drain can be removed. Each center is allowed to remove drain on whatever POD after a negative test. Drain management in patients with a suspicious debt or positive blue test is left to center preference (no further blue tests are planned). Postoperative complications are recorded until POD 30 or in hospital if hospital stay is longer than 30 days.

Reoperation under general anesthesia and/or percutaneous abdominal/thoracic drain placement during the first 30 PODs for any cause related to the previous gastrectomy is considered as an event in both groups. The cause-effect relationship decision is left to the lead site surgeon and in case of doubt, the investigator can ask for support from the steering committee. This specification was considered mainly necessary in case of unrelated pathology acquired after discharge but within POD 30 (e.g., operation for road accident). After discharge, patients are evaluated in the outpatient clinic on POD 30 or in the subsequent week. Follow-up calls are conducted by authorized medical or nursing staff at POD 60 ± 7 and 90 (max + 7 days) in order to assess patient’s clinical status.

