#### Statistical analysis

Categorical variables will be presented as absolute and percent frequencies, continuous variables as mean and standard deviation when approximately symmetrically distributed, and as median and interquartile range otherwise.

The proportion of patients undergoing re-intervention or percutaneous drain placement (primary endpoint) will be computed for each group. The difference between the primary end-point proportion in the treated group and in the control group will be computed with the corresponding confidence interval. If the upper limit of the 90% confidence interval of this proportion does not exceed the non-inferiority margin difference of 3.56%, the null hypothesis of inferiority will be rejected.

Further statistical analysis on the primary endpoint will follow a hierarchical approach: if the non-inferiority null hypothesis will be rejected, significance of differences in the primary endpoint between control and experimental arms will be further investigated with a Fisher’s exact test. The relation between the primary endpoint and treatment (drain placement or avoidance) will be further investigated using a multivariable Firth’s logistic model, adjusting for center, sex, age, tumor stage, and type of gastrectomy (total/subtotal).

To evaluate significance of differences between control and experimental arms, Fisher’s exact test or chi-square test will be used for nominal variables (reoperation, placement of additional percutaneous drain, anastomotic or duodenal stump fistula, postoperative mortality, hospital readmission), Wilcoxon-Mann-Whitney test for ordinal variables (fistula or complication severity), and *t* test (or the corresponding non-parametric test) for continuous variables (length of hospital stay, time from surgery to fistula detection). Statistical significance for secondary analyses will be set at *p* < 0.05 and statistical tests will be two-sided.

Statistical analyses will be performed using Stata®/IC 16.0 for windows (StataCorp LLC, College Station, TX, USA).

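### Leak incidence and time to diagnosis are tested between arms although only the drain arm has protocol-defined leak surveillance, so diagnosed leaks mix occurrence with detection and the time test compares differently selected subsets

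*Protocol article*

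**What the plan says.** **Surveillance.** The section Postoperative procedure says of the drain arm: "Prophylactic drain in group A patients is daily evaluated checking for suspicious debt". When output is normal, a methylene blue test is done on POD 4, and "the test is considered negative if no blue staining of drain output is apparent within 60 min". Under Operation and intraoperative dropout, group B receives no drain. For everything else, "All patients follow the usual postoperative pathway of each participating center except for abdominal drain management". The article describes no leak assessment common to both arms.

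**Endpoints.** Outcomes lists incidence, severity and time to diagnosis of anastomotic and duodenal leak as the first secondary endpoint. The abstract's Methods paragraph puts "incidence and time for diagnosis of anastomotic and duodenal leaks, length of hospital stay, and readmission rate" among the secondary endpoints assessed for superiority.

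**Tests.** Statistical analysis assigns Fisher's exact or chi-square to nominal outcomes, including "anastomotic or duodenal stump fistula, postoperative mortality, hospital readmission". It assigns a t test, or its non-parametric counterpart, to "length of hospital stay, time from surgery to fistula detection". Secondary tests are two-sided at p < 0.05. The Blinding section says that care is unblinded after the operation.

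**The concern.** A drain treats, but it also detects. The Background names early diagnosis as a main reason drains have been advocated. Two problems follow from the tests as written.

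- **Incidence.** A minor leak that shows only as suspicious drain fluid or blue staining can be counted in group A, while the same leak can go uncounted in group B. The raw comparison then tends towards fewer leaks without a drain, the direction that favours the experimental arm, even if leaks occur equally often.
- **Time.** Time to detection exists only for patients whose leak was diagnosed. That group is formed after randomisation, and the assigned strategy affects who enters it. Randomisation does not protect the comparison.

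At stake is a secondary superiority claim about leaks, or about speed of diagnosis, that could be published as a clinical effect when part or all of it comes from how leaks were looked for.

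**Working it through.** **The plan's own figure.** The article gives no figure for the leak endpoints. Its sample size for the primary endpoint supplies the arm size, and it reproduces. The distance to the margin is 0.0356 + (0.0644 − 0.0416) = 0.0584. The unpooled variance sum is 0.0644 × 0.9356 + 0.0416 × 0.9584 = 0.1001. With one-sided alpha 5% and 80% power, n = (1.645 + 0.842)² × 0.1001 / 0.0584² ≈ 182 per arm, as stated.

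**Incidence: inputs.** n = 182 per arm is from the article. The rest is assumed, because the article gives neither quantity: a true leak rate p, equal in both arms, of 5% or 8%, and a fraction s of 20% or 40% of leaks detectable only through a drain. Group A then observes p and group B observes p(1 − s).

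**Incidence: method.** The probability that a two-sided Fisher test gives p < 0.05 is the sum, over all pairs of counts (i, j) that the test calls significant, of Bin(i; 182, p) × Bin(j; 182, p(1 − s)).

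| True rate, both arms | Detectable only through a drain | Observed A v B | Expected diagnosed leaks A v B | Significant |
|---|---|---|---|---|
| 5% | 0 | 5% v 5% | 9.1 v 9.1 | 2.7% |
| 5% | 20% | 5% v 4% | 9.1 v 7.3 | 4.2% |
| 5% | 40% | 5% v 3% | 9.1 v 5.5 | 10.0% |
| 8% | 0 | 8% v 8% | 14.6 v 14.6 | 3.1% |
| 8% | 20% | 8% v 6.4% | 14.6 v 11.6 | 6.0% |
| 8% | 40% | 8% v 4.8% | 14.6 v 8.7 | 17.6% |

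With unequal detection, nearly all the significant results show more leaks with a drain. The apparent risk ratio is 1/(1 − s), that is 1.25 to 1.67, with no true difference.

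**Time: selection alone.** Suppose clinically apparent leaks are diagnosed at the same mean day T in both arms, and the drain-only leaks are found at the POD 4 test. The mean among diagnosed leaks is T in group B and (1 − s)T + 4s in group A. The difference is s(T − 4). With s = 0.2 to 0.4, group A looks 0.2 to 0.4 days faster for each day that T lies beyond POD 4, although no clinically apparent leak was found sooner. On the assumed rates, the test would rest on about 5 to 15 diagnosed leaks per arm.

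**The obvious alternative definition.** Restricting the test to Clavien-Dindo grade III or higher was checked in the same way. Take the 4.8% of clinically apparent leaks from the last row, and assume that half of group A's avoid a procedure because a drain is already in place. The observed rates are then 2.4% v 4.8%, which is significant in 14.7% of trials, almost always against omitting the drain.

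**The case against.** **Earlier diagnosis is what a drain is for.** The trial randomises strategies, and drain surveillance is part of one of them. A reader might infer that faster diagnosis in group A would be nothing but an artefact. The article does not support that, since its Background presents early diagnosis as a purpose of the drain. What stands against the plan is narrower: a comparison confined to diagnosed leaks cannot separate finding the same leaks sooner from finding additional ones.

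**The size is assumed.** This is true. At 20% drain-only detection the excess is small (4.2% and 6.0%); only the 40% case at an 8% leak rate reaches 18%. The calculation also assumes that group B never detects these leaks. Centres may test for leaks in both arms under their usual pathway, which would narrow the gap; the article does not say. The blue test concerns anastomotic leak, so for duodenal leaks the asymmetry is mainly the daily check.

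**Grading already helps.** Leaks are classified by a consensus list, graded by Clavien-Dindo, and compared on severity. An excess of minor leaks in group A could therefore be seen. But grading standardises the label, not the search, and the incidence test still counts every diagnosed leak.

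**Grade III+ is no clean substitute.** This also stands. It brings a bias in the opposite direction of similar possible size, and it overlaps a primary endpoint of reoperation or percutaneous drainage. It can support the leak analysis but should not replace it.

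**An unseen analysis plan may deal with it.** The article itself fixes the tests and the superiority reading, so the point concerns what is stated.

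**Conclusion.** The point holds, for secondary endpoints only. The surveillance is prescribed in one arm, and the between-arm leak tests take no account of it. With equal true leak rates of 5-8%, 20-40% of leaks detectable only through a drain and 182 per arm, the incidence test is significant in about 4-18% of trials, against about 3% with equal detection. Those rates and fractions are assumptions, so the range shows what could happen and is not an estimate of the bias in this trial. For time to diagnosis, the defect is the leak-only subset, not the idea that a drain may bring diagnosis forward.

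A reader might go further and infer that the trial's main conclusion is compromised. The article does not support that: the primary endpoint counts procedures and is not defined by leak detection.

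**What to change.** Change the analysis wording as follows; care and the primary endpoint stay as they are.

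1. Report all-grade leak incidence by arm, with grade and mode of detection (drain output or blue test only, versus clinical or imaging). Do not claim superiority in leak occurrence from the all-grade test.
2. Show Clavien-Dindo grade III+ leaks as a supporting comparison. State that a drain already in place may spare a group A patient a grade III procedure, so that its bias runs against drain omission, and that it overlaps the primary endpoint.
3. Replace the leak-only t test or rank test with the cumulative incidence of leak diagnosis in all mITT patients by arm, with death as a competing event. Read it as an effect of the strategy including its surveillance. Give time among diagnosed leaks descriptively.

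Cost: one less formal secondary superiority claim and a little more analysis work. Grading is already collected. Confirm that the case report form records how each leak was found, which the article does not state.

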### Outcomes

The primary composite endpoint is the cumulative incidence of reoperation and/or percutaneous drainage placement by the 30th postoperative day.

Secondary endpoints are as follows:
Incidence, severity, and time to diagnosis of anastomotic and duodenal leakLength of hospital stayOverall 30 days morbidity or in hospital if longer than 30 daysOverall 90 days mortality30 days readmission rate

Length of hospital stay is considered from the day of operation until discharge at home or at other facilities, or death. Postoperative complications, including anastomotic and duodenal leak, are classified according to the International Consensus on a Complications List After Gastrectomy for Cancer [23] and stratified by severity using the Clavien-Dindo classification [24].

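### Leak incidence and overall morbidity are compared for superiority although leak surveillance is scheduled in the drain arm only, so these secondary results may favour omission with no true difference

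*Protocol article*

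**What the plan says.** The protocol article's Postoperative procedure section sets the surveillance. In group A, "Prophylactic drain in group A patients is daily evaluated checking for suspicious debt". A second check is scheduled for those whose output looks normal; it "is performed on postoperative day (POD) 4 and the test is considered negative if no blue staining of drain output is apparent within 60 min". Being read from drain output, this methylene blue test needs a drain, and it is described as an indirect sign about the anastomosis. Group B has no drain. For everything else the rule is "All patients follow the usual postoperative pathway of each participating center except for abdominal drain management", and no scheduled leak check is stated for group B.

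The Abstract (Methods) gives the purpose of the secondary endpoints: "Secondary endpoints assessed for superiority are overall morbidity and mortality, Comprehensive Complications Index, incidence and time for diagnosis of anastomotic and duodenal leaks". The Outcomes section says "Postoperative complications, including anastomotic and duodenal leak, are classified according to the International Consensus on a Complications List After Gastrectomy for Cancer", with Clavien-Dindo grading on top. It sets no minimum grade and no condition on how a leak came to light.

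The Statistical analysis section assigns Fisher's exact or chi-square tests to nominal variables, among them "anastomotic or duodenal stump fistula", two-sided at 0.05. Overall morbidity is not named in that list, but as a yes/no variable it would fall under the same tests. Nothing there deals with unequal detection. The Blinding section states that there is no blinding after the operation.

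**The concern.** The control intervention is also a measuring instrument for a secondary endpoint. The Background section itself presents the drain as having been advocated mainly as a means of finding and treating leaks early. A leak that shows only as abnormal drain output or blue staining can be recorded in group A. The same leak in group B may never be recorded unless it produces symptoms or the centre's usual pathway happens to look for it.

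Extra recorded leaks raise leak incidence in the drain arm and, because leaks are postoperative complications, overall morbidity as well. Both comparisons then lean towards omission even if the true leak rates are equal. The Objectives section says that omission would be favoured once inferiority is rejected, because a drain may be harmful. A significant excess of leaks or morbidity with a drain would be read as support for that, although part of it could be an effect of looking harder.

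**Working it through.** **Surveillance by arm**

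| | Group A (drain) | Group B (no drain) |
|---|---|---|
| Daily check of drain output | yes | not possible |
| Day-4 dye test read from drain output | yes, if output is normal | not possible |
| Centre's usual pathway | yes | yes |
| Other scheduled leak check | none stated | none stated |

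The dye test bears on the anastomosis. For the duodenal stump, the asymmetry comes mainly from daily inspection.

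**The plan's own figure.** The protocol states no leak rate, so no stated figure bears on the point. The design's patient numbers do reproduce. With the unpooled formula, n = [0.0644×0.9356 + 0.0416×0.9584] × (1.645 + 0.842)² / (0.0356 + 0.0228)² = 181.5, hence 182 per arm as stated, or 202 per arm with dropout. The calculation below uses 202, with 182 as a check.

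**Model.** Let L be the true leak rate, equal in both arms, and s the share of leaks found only through the drain. Neither is in the documents. I assume L = 5-8% and s = 20-40%.

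- Recorded rate: group A, L; group B, L×(1−s).
- Apparent difference: L×s.
- Apparent relative risk, no drain versus drain: 1−s.

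Low end: 5% × 20% = 1.0 point, or 0.010 × 202 = 2.0 patients. High end: 8% × 40% = 3.2 points, or 0.032 × 202 = 6.5 patients.

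**Chance of a falsely significant result favouring no drain.** I enumerated Fisher's exact test over all pairs of binomial counts, two-sided 0.05, counting only results with more leaks in group A:

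| L | s | Recorded A vs B | 202 per arm | 182 per arm |
|---|---|---|---|---|
| 5% | 0 | 5.0% vs 5.0% | 1.5% | 1.4% |
| 5% | 20% | 5.0% vs 4.0% | 4.3% | 3.8% |
| 5% | 40% | 5.0% vs 3.0% | 11.4% | 9.9% |
| 8% | 0 | 8.0% vs 8.0% | 1.6% | 1.5% |
| 8% | 20% | 8.0% vs 6.4% | 6.3% | 5.7% |
| 8% | 40% | 8.0% vs 4.8% | 19.8% | 17.6% |

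The plan also allows chi-square, which is less conservative. At L = 5%, s = 25% and 182 per arm, the normal approximation gives 8.4% where Fisher's test gives 4.9%.

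**Overall morbidity.** The effect is diluted. Take a morbidity of 20-40% (assumed) and 182 per arm, and suppose each extra recorded leak falls in a patient with no other complication. Then 1 extra point in group A gives about a 4% chance of false significance favouring no drain, and 2.5 extra points gives 7-8%, against a nominal 2.5% (normal approximation).

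**The case against.** **Detection is part of what a drain does.** Early diagnosis is a stated purpose of the drain, and time to diagnosis is itself an endpoint. This stands: the asymmetry cannot be removed. It does not justify reading raw recorded counts as a difference in the number of leaks.

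**The counting rule is not fully visible.** Leaks are classified by a consensus list that the article does not reproduce. Whether a symptomless, untreated finding in the drain counts as a leak may be settled there or on the case report form. This stands, and it is why the size is unknown. The article's own wording sets no such limit.

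**Other analyses would expose an artefact.** Severity is compared, reoperation and percutaneous drainage are tested separately, and the Comprehensive Complications Index weights severity. This helps in part. But extra mild leaks in group A would make that arm's leaks look milder on average, so the severity comparison is affected by the same gap, and the incidence test would still be reported.

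**Stronger readings that the documents do not support.**
- A reader might infer that silent leaks can count in one arm only. Usual pathways apply to both arms and may include leak checks, so such leaks are less likely to be recorded in group B, but recording them there is not impossible.
- A reader might take it as given that a drain cannot alter how many leaks occur. The Objectives section treats the drain as possibly harmful, so a true difference is a fair question. Equal rates are an assumption of the calculation above.
- A reader might add false-positive dye tests to the leak count. Nothing says that a positive test is recorded as a leak. It guides drain removal, and what follows a positive test is left to the centre.
- A reader might extend the bias to the non-inferiority conclusion. That endpoint counts reoperations and percutaneous drainage, not detected leaks.

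**Conclusion.** The concern holds for two secondary comparisons, leak incidence and overall morbidity. The protocol schedules leak surveillance in one arm and tests both endpoints for superiority with no condition on severity or mode of detection, so the plan as written can favour omission when nothing differs.

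The direction follows from the text, but the size does not. Over the assumed range, the false-significance risk for leaks runs from a modest rise at the low corner to roughly twelve times the no-gap level at the high corner (19.8% against 1.6%). Overall morbidity is less affected. All of this assumes equal true leak rates and one drain-only share for anastomotic and duodenal leaks together. The sample size, power and alpha of the primary analysis are unchanged. The point is worth correcting but does not threaten the trial's main conclusion.

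**What to change.** In Outcomes and Statistical analysis:

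1. Record for each leak how it was first detected, if the case report form does not already do so.
2. Base the between-arm leak comparison, and the leak component of overall morbidity, on leaks that caused symptoms or received any treatment for the leak. Treatment should include management through a drain already in place. Use the same definition in both arms, regardless of how the leak was first found.
3. Report the all-leak comparison as supportive.
4. List symptomless, untreated leaks found only by drain output or dye test descriptively.

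Neither Clavien-Dindo grade III or higher nor imaging prompted by clinical signs should be the sole criterion. An existing drain may spare a group A leak a procedure that the same leak in group B would need, and group A imaging may be prompted by drain output. Either rule would tilt the comparison the other way.

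The cost is endpoint wording and at most one data item. Patient care, sample size and the primary analysis stay as they are. Fewer leaks enter the comparison, and some detection difference remains, because early detection through the drain may itself trigger treatment.
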